### Statistical analysis

Analyses will be according to intention to treat. The effect of removal of incentives and removal of feedback on chlamydia testing rates will be investigated by comparing the study groups as shown in the table below (Table 1). We will also investigate the effect of each of the two interventions on chlamydia testing rates as main effects exploiting the factorial nature of the design. Thus, the effect of removing financial incentives will be assessed by comparing randomised groups 2 and 3 with groups 1 and 4. Similarly, the effect of removing audit plus feedback will be assessed by comparing groups 1 and 3 with groups 2 and 4. The advantage of a factorial design is that it includes all patients in assessing the effectiveness of the two separate interventions, maximising the power of the study. However, this is based on the assumption that the effect of the two interventions is at least additive, and that there is no negative interaction between them, which will be tested. Formal statistical comparisons will be based on generalised mixed models that can account for cluster (general practice), GP and patient variability. Generalised estimating equation (GEE) approaches, with robust standard errors, will be adopted using STATA software. Hierarchical logistic regression models will be used to examine the impact of each of the two interventions over time on the proportion of patients who have a chlamydia test during the follow-up. Analyses will be adjusted for the chlamydia testing rate at each general practice immediately prior to commencing ACCEPt-able.

**Table 1 Tab1:** Comparison of groups for analysis

Comparison	Removal of audit and feedback—continue financial incentives only	Removal of financial incentives—continue audit plus feedback only	Removal of financial incentives and audit plus feedback	Continue financial incentives and audit plus feedback
	Group 1	Group 2	Group 3	Group 4
Removal of financial incentives versus other	Groups 2 and 3 versus groups 1 and 4			
Removal of audit and feedback versus other	Groups 1 and 3 versus groups 2 and 4			

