### Sample size

The intra-cluster correlation for chlamydia testing in participating general practices in the 12 months prior to commencing ACCEPt-able was 0.02. The cluster size of an average of 700 patients aged 16 to 29 years seen in each participating general practice per year gives a design effect of 15. With 60 general practices available for randomisation and an average of 700 patients per practice, we get an effective sample size of 2800 (calculated by dividing total patients by design effect = 60 × 700 = 42,000; 42,000/15 = 2800). A sample size of 2800 patients across all four study groups will allow us to detect a 5 % decrease in testing from 20 to 15 % between any two groups with 94 % power. A total of 15 general practices will be randomly allocated to each of the four study arms.

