This trial has several strengths. Firstly, a factorial RCT design is the most powerful and efficient method to investigate the impact of removing financial incentives and audit plus feedback on GP behaviour. In addition to the effects of each treatment, factorial design provides some data on the interaction that may exist between two interventions. Hence, we will have evidence about whether the effect of the removal of incentives varies according to whether or not practices receive audit plus feedback as well. Secondly, the inclusion of qualitative interviews will collect valuable data about the perceived importance of incentive payments and audit and feedback to general practice staff. These qualitative data will be assessed alongside the trial results, providing greater insight to the RCT results. Finally, the cost-consequence analysis also strengthens this trial. This trial will gather evidence to inform future policy on primary care reform, and as part of this, the cost of the interventions investigated and the outcomes associated with each intervention are of paramount importance to decision makers. A cost-consequence analysis involves itemising the different intervention components and their costs and the outcomes (chlamydia testing rate) for each trial group. We have selected this form of analysis because, unlike a cost-effectiveness analysis, the cost-consequence approach clearly lists the costs and outcomes associated with each intervention enabling decision makers to see the actual data. Unfortunately, one clinic refused to participate in the trial. However, this has negligible impact on our statistical power as we will still have 93 % power to detect a drop in chlamydia testing rates from 20 to 15 % between any two groups.

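### The 94 % and 93 % power stated for any pair of groups holds only for the two factorial main effects; a comparison of two single arms has about 69 %

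*Protocol article*

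**What the plan says.** The Sample size section of the Protocol article derives an effective sample of 2800 patients over four arms of 15 practices each. It says that this will "detect a 5 % decrease in testing from 20 to 15 % between any two groups with 94 % power". The Discussion, allowing for the one practice that declined, says: "we will still have 93 % power to detect a drop in chlamydia testing rates from 20 to 15 % between any two groups".

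The Statistical analysis section refers the reader to Table 1 for the comparisons. Table 1 has two rows: removal of incentives (groups 2 and 3 against 1 and 4) and removal of audit plus feedback (groups 1 and 3 against 2 and 4). The section then continues: "We will also investigate the effect of each of the two interventions on chlamydia testing rates as main effects exploiting the factorial nature of the" …, and describes the same two comparisons again in prose. It notes that the factorial analysis assumes at least additive effects and that "there is no negative interaction between them, which will be tested". The article states no significance level.

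**The concern.** In a four-arm trial, power between any two groups means power for a comparison of one arm with another, such as group 2 with group 4. Table 1 contains no such comparison. The word *also* before the main effects adds to the doubt, because it suggests that Table 1 holds something else, when the main effects are all it holds.

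A single-arm comparison uses half the patients that a main effect uses, so one power figure cannot serve both. A reader who trusts the stated figure could take a non-significant result for group 2 against group 4 as good evidence that testing is sustained without incentives, when the chance of missing a 5-point fall is about 31 % rather than 6 %. The risk is greatest if the interaction test suggests that the effects are not additive, because attention then moves from the main effects to single-arm comparisons.

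**Working it through.** **Inputs, all from Sample size unless noted**
- Testing rates 20 % and 15 %, a difference of 0.05.
- Intra-cluster correlation, which "in the 12 months prior to commencing ACCEPt-able was 0.02".
- An average of 700 patients aged 16 to 29 "seen in each participating general practice per year gives a design effect of 15".
- 60 practices, 15 per arm; 59 recruited (Trial status).
- Significance level: not stated. Assumed two-sided 5 %.

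**Step 1: design effect and effective sample**

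Design effect = 1 + (700 − 1) × 0.02 = 14.98, rounded to 15 in the article. Effective total = 60 × 700 / 15 = 2800. This gives 2800 / 4 = 700 per arm, and 2800 / 2 = 1400 on each side of a main effect. With 59 practices the total is 59 × 700 / 15 = 2753, so about 1377 per side of a main effect and 688 per arm (treating the odd number as evenly split).

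**Step 2: formula**

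With p̄ = (0.20 + 0.15) / 2 = 0.175,

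power = Φ{ [0.05 − 1.96 × √(2 × 0.175 × 0.825 / n)] / √[(0.20 × 0.80 + 0.15 × 0.85) / n] },

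where n is the effective number on each side.

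**Step 3: reproduce the article's figure with a main effect (n = 1400)**

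- Standard error under the null: √(0.28875 / 1400) = 0.01436.
- Standard error under the alternative: √(0.2875 / 1400) = 0.01433.
- (0.05 − 1.96 × 0.01436) / 0.01433 = 1.52, so power = 93.6 %, the article's 94 %.

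**Step 4: two single arms (n = 700)**

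- Standard errors: √(0.28875 / 700) = 0.02031 and √(0.2875 / 700) = 0.02027.
- (0.05 − 1.96 × 0.02031) / 0.02027 = 0.50, so power = 69.3 %.

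**Step 5: results together**

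| Comparison | 60 practices | 59 practices | Article states |
|---|---|---|---|
| Main effect, two arms against two | 93.6 % | 93.3 % | 94 %, 93 % |
| One arm against another | 69.3 % | 68.5 % | 94 %, 93 % |

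**Step 6: could another convention rescue the single-arm reading?**

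For 700 against 700, a one-sided 5 % test gives 79.4 %, an unpooled variance 69.4 % and a continuity correction 66.7 %. None comes near 94 %. For 1400 against 1400, the unpooled variance gives 93.7 % and the continuity correction 93.0 %. The stated figures therefore belong to the main effects.

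**The case against.** The strongest reply is that the plan is clear where it matters. Table 1 and the prose after it define exactly two effect comparisons, they match the first two trial objectives, and the power was evidently calculated for them. On this view the phrase in the power statements is a loose label. Most of this stands. It is why the correction is one of wording and not of design: the sample size is adequate for the listed comparisons. It does not make the power statements true as written, and the article makes the claim twice.

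A reader might go further and infer three stronger points. The article does not support them.

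- *That no deciding contrast is given, and the family-wise false-positive rate is about 10 % to 23 %.* The upper end counts six pairwise tests, two main effects and the interaction as confirmatory. The analysis section lists no pairwise tests, and no level is stated for any test. For the two listed contrasts at 5 % each, the rate is 1 − 0.95² = 9.75 %. Whether to adjust across two separate objectives in a factorial trial is a matter of judgement.
- *That the missing hierarchy or multiplicity rule is itself an error.* Such rules are commonly left to the statistical analysis plan or full protocol, neither of which is shown.
- *That the candidate contrasts lead to opposite conclusions.* With a purely additive incentive effect and no feedback effect, simulation gives different significance verdicts for the main effect and for group 2 against group 4 in 31 %, 34 % and 26 % of trials, for true falls of 3, 4 and 5 points. Both contrasts then estimate the same quantity. The disagreement reflects mainly the lower precision of the single-arm pair. Opposite true effects would need a qualitative interaction.

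**Conclusion.** The point holds as an error in a stated property of the design. The power claimed for any pair of groups is about 24 percentage points too high for a single-arm pair (93.6 − 69.3 = 24.3; with 59 practices, 93.3 − 68.5 = 24.8). It is correct for the two main effects in Table 1. The wording of the Statistical analysis section adds to the confusion by presenting those main effects as additional to a table that contains nothing else.

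The result rests on the article's own design effect of 15, equal arms, and a two-sided 5 % level, which is assumed but reproduces both stated figures. The main-effect power also takes the 5-point fall as the average over both levels of the other factor. If, for example, groups 1, 2 and 3 were all at 15 % and only group 4 at 20 %, the incentive main effect would be (0.15 + 0.20)/2 − (0.15 + 0.15)/2 = 2.5 points, with 43.5 % power.

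Nothing here shows that the trial is too small for its two listed comparisons, or that it carries an inflated false-positive rate of 20 % or more.

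**What to change.** 1. In Sample size, where the text reads "from 20 to 15 % between any two groups with 94 % power", attach the power to each of the two main-effect comparisons in Table 1, and state the significance level used. Make the same change to the 93 % statement in the Discussion.
2. In both places, add that a comparison of two single arms has about 69 % power for the same fall.
3. In Statistical analysis, delete *also* from the sentence on main effects and name the two Table 1 comparisons as the primary contrasts. Describe the interaction and any single-arm contrasts as secondary.

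The change takes a few sentences and needs no further practices or data. Its only cost is a less favourable stated power for pairwise comparisons. No multiplicity adjustment is required by this point.

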### Trial status

The trial has been registered on the Australian and New Zealand Clinical Trials Registry (ACTRN12614000595617). A total of 59 general practices have been recruited to ACCEPt-able with only one eligible practice refusing to participate (98 % response rate). The intervention period will be complete on 2017 with trial results due late 2017.

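### Table 1's pooled contrasts equal the effect of removing one component alone only if there is no interaction in either direction; the stated assumption is weaker, and no contrast with group 4 alone is listed

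*Protocol article*

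**What the plan says.** The Statistical analysis section of the protocol article refers to Table 1 for the group comparisons and then adds main effects that use the factorial structure. Both rows of Table 1 are pooled margins: groups 2 and 3 against 1 and 4 for incentives, and groups 1 and 3 against 2 and 4 for audit plus feedback. The gain in power from using all patients is qualified: "this is based on the assumption that the effect of the two interventions is at least additive, and that there is no negative interaction". The article says that this will be tested. The model is logistic and adjusts for each practice's prior testing rate.

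The Discussion says of the interaction that "we will have evidence about whether the effect of the removal of incentives varies according to whether or not practices receive audit plus feedback". The stated aim covers removal of incentives, of feedback, or of both, and the cost-consequence section compares all four scenarios separately.

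**The concern.** A pooled margin averages two effects: removing a component while the other continues, and removing it when the other has gone too. A funder who asks what happens if incentives stop but feedback stays needs the first of these. The average equals it only when the two agree, that is, when there is no interaction of either sign. The stated condition excludes one sign and allows the other.

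It also leaves open whether the interventions are the components as provided or their removal, which is what this trial randomises. The reading matters. Components that can stand in for each other are less than additive when provided but more than additive when removed.

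At stake is what the trial can conclude about single removal and joint removal. Table 1 has no row that estimates either one directly.

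**Working it through.** **Inputs.** From the Sample size section: "The intra-cluster correlation for chlamydia testing in participating general practices in the 12 months prior to commencing ACCEPt-able was 0.02"; "700 patients aged 16 to 29 years seen in each participating general practice per year gives a design effect of 15"; "we get an effective sample size of 2800"; "A total of 15 general practices will be randomly allocated to each of the four study arms". From Trial status: "A total of 59 general practices have been recruited to ACCEPt-able". My assumptions, because the article gives no figure: two-sided 5 % level, and an interaction of 5 points, the same size as the planned effect.

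**1. Reproduce the plan's power.** The article claims that the trial can "detect a 5 % decrease in testing from 20 to 15 % between any two groups with 94 % power".
- Design effect: 1 + 699 × 0.02 = 14.98, or about 15. Effective sample: 60 × 700 / 15 = 2800, so 700 per group and 1400 per pooled margin.
- Pooled margins: SE = √[(0.16 + 0.1275)/1400] = 1.43 points; 5/1.43 = 3.49; power = Φ(3.49 − 1.96) = 94 %. The figure reproduces here.
- Two single groups: SE = √[(0.16 + 0.1275)/700] = 2.03 points; 5/2.03 = 2.47; power = Φ(0.51) = 69 %.

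**2. What the pooled contrast estimates.** Let p1 to p4 be the group testing rates and I = p4 − p1 − p2 + p3 the interaction. The pooled effect of removing incentives is

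½[(p2 − p4) + (p3 − p1)] = (p2 − p4) + I/2.

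It differs from the single-removal effect p2 − p4 by half the interaction, whatever its sign. The same holds for feedback, with p1 − p4.

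**3. Two patterns with a 5-point interaction.**

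| Groups 4/1/2/3 (%) | Each single removal v group 4 | Both removed v group 4 | Each pooled effect |
|---|---|---|---|
| 20/20/20/15 | 0 | −5 | −2.5 |
| 20/15/15/15 | −5 | −5 | −2.5 |

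The pooled results are identical, but the policy conclusions are opposite. Read as removals, the first pattern is more than additive and meets the stated assumption. Read as components provided, the second does: each alone adds nothing to 15 %, and both together add 5. So on either reading, a pattern that meets the assumption still misstates single removal.

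**4. Power of the interaction test.** Var(I) = Σ p(1 − p)/700, four times the variance of a main effect.
- 20/15/15/15: SE = √(0.5425/700) = 2.78 points; 5/2.78 = 1.80; power 43 % (39 % on the logit scale).
- 20/20/20/15: SE = √(0.6075/700) = 2.95 points; 5/2.95 = 1.70; power 40 % (43 % on the logit scale).
- With 59 practices and a t reference, power is 38–42 %.
- The interaction detectable with 80 % power is about 8 points.
- For comparison, 20/20/20/10 has I = −10: SE = √(0.57/700) = 2.85 points; 10/2.85 = 3.50; power 94 %.

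**5. Baseline adjustment.** If r is the practice-level correlation between baseline and outcome, each group contributes p(1 − p)[0.02(1 − r²) + 0.98/700]/15 to the variance. Across the two patterns, power becomes 49–54 % at r = 0.5, 64–69 % at r = 0.7 and 76–81 % at r = 0.8. The article does not give r.

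**6. Scale.** Rates of 20/15/15/10 % are exactly additive in percentage points but have a log-odds interaction of −0.11. Additivity therefore has no definite meaning until a scale is named, and the planned model is logistic.

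**The case against.** The strongest reply is that the assumption is attached to a sentence about power. As a condition for keeping power it is defensible, because a more-than-additive pattern does not dilute the main effect. That stands. But the same paragraph uses the pooled contrasts to assess each removal, and the condition does not suffice for that use.

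Three further points carry weight.
- An average over the other factor is a legitimate quantity and fits the first two objectives as worded.
- The article plans an interaction test, and it plans testing rates for each group in the cost-consequence work. Its wording also suggests group comparisons besides the main effects, although Table 1 shows none.
- Weak interaction tests are usual in 2×2 trials sized on main effects. The Discussion promises only some data on interaction, so asking for a power statement or softer wording there would be reporting preference.

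Two stronger readings are tempting, and the documents support neither. A reader might infer that the test would miss any pattern that makes pooling misleading. It would not: a 10-point interaction such as 20/20/20/10 % is found with about 94 % power (98 % on the logit scale). A reader might also infer that a non-significant test will be taken as permission to pool. The article states no such rule, and how the result will be used may be set out in an analysis plan that is not shown.

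**Conclusion.** The point holds as one of interpretation and of listed contrasts. The stated assumption does not make the pooled contrast equal to the effect of removing one component while the other continues. In the two patterns shown, the error is 2.5 points, half of the 5-point effect for which the trial was sized. The interaction test would miss either pattern more often than not, at about 40–43 % power. That figure assumes a 5-point interaction, an effective sample of 700 per group, a two-sided 5 % level and no gain from baseline adjustment. It is like for like with the article's 94 %, which is also unadjusted, and it would be materially higher if prior and later testing rates are strongly correlated. The main effects remain valid as averages. What is missing from Table 1 is the set of contrasts that answers the and/or part of the aim.

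**What to change.** - State the assumption as no interaction in either direction, and name the scale (risk difference or log odds).
- Add three rows to Table 1: 1 v 4 (feedback removed, incentives kept), 2 v 4 (incentives removed, feedback kept) and 3 v 4 (both removed).
- Report these with the interaction estimate and its 95 % confidence interval beside the main effects, whatever the interaction p-value, and do not take a non-significant test as evidence of additivity.

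The cost is a change of wording and three extra estimates from the same model; no new data are needed. The new contrasts are less precise. For 20 v 15 %, the 95 % interval is about ±4.0 points (1.96 × 2.03) against ±2.8 for a pooled margin (1.96 × 1.43), and power is about 69 % instead of 94 %.

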### Design of ACCEPt-able

ACCEPt-able is a factorial cluster RCT (Australian and New Zealand Clinical Trials Registry ACTRN 1261400059617) with the general practice being the unit of randomisation. An RCT has a factorial design when two or more experimental interventions are not only evaluated separately but also in combination and against a control [23]. The strength of this design is that it provides more information than parallel designs. Our intervention is allocated at the cluster level (general practice) because patients attending each practice can consult with multiple different GPs over time but they are only eligible for one chlamydia test each year unless they report additional risk factors for infection (e.g. recent change in sex partner) or genital symptoms requiring further chlamydia testing.

Practices were recruited into ACCEPt-able when their participation in ACCEPt was completed. A research officer explained the trial to the GPs and once the GPs consented to participate, the practices were randomised to one of four groups. (Fig. 1).

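### Mixed models and GEE are both assigned to the formal comparisons and neither is named primary; with standard robust errors and a z test, GEE on 59 practices would run at about 6–8% type I error for the Table 1 contrasts

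*Protocol article*

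**What the plan says.** All the modelling text is in Statistical analysis in the protocol article.

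- Model for the comparisons: "Formal statistical comparisons will be based on generalised mixed models that can account for cluster (general practice), GP and patient variability".
- The sentence after it: "Generalised estimating equation (GEE) approaches, with robust standard errors, will be adopted using STATA software".
- The sentence after that has its own purpose: "Hierarchical logistic regression models will be used to examine the impact of each of the two interventions over time".
- Covariate: "Analyses will be adjusted for the chlamydia testing rate at each general practice immediately prior to commencing ACCEPt-able".
- Contrasts, repeated in Table 1: "the effect of removing financial incentives will be assessed by comparing randomised groups 2 and 3 with groups 1 and 4", and "the effect of removing audit plus feedback will be assessed by comparing groups 1 and 3 with groups 2 and 4".

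Trial status gives the number of clusters: "A total of 59 general practices have been recruited to ACCEPt-able". The section on randomisation says allocation was by minimisation on two variables, the practice's testing rate in the previous 12 months and its size. Only the first appears in the planned adjustment.

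**The concern.** Two statements of intent cover the same formal comparisons. A logistic mixed model estimates an odds ratio conditional on the practice, usually with model-based standard errors. Logistic GEE estimates a population-averaged odds ratio with a sandwich variance. The estimates, intervals and p-values differ, and nothing ranks one above the other. An analyst could fit both and report either as the planned analysis.

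The second issue is the size of the test if GEE is chosen. The sandwich variance is estimated from residuals that have been pulled towards the fitted model, so it is too small when clusters are few. Here the Table 1 contrasts set about 30 practices against 29, and a comparison of two single groups would set about 15 against 14. Practice-level covariates and unequal practice sizes make the bias worse. At stake is whether a result reported at the 5% level really has a 5% false-positive rate.

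**Working it through.** **Inputs from the article.** 59 practices (Trial status); ICC 0.02, mean 700 patients per practice, 20% tested (Sample size); baseline testing rate as covariate (Statistical analysis).

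**Assumed, because the article does not give them.** Two-sided 5% level; groups of 15, 15, 15 and 14; coefficient of variation (CV) of practice size 0, 0.5 or 0.8; correlation 0.6 between a practice's baseline and follow-up rates; working correlation exchangeable or independence.

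**The plan's own figures.** Design effect 1 + (700 − 1) × 0.02 = 14.98. Effective sample 60 × 700 / 15 = 2800. Power for 20% v 15% with 1400 per side:

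- null SE = √(2 × 0.175 × 0.825 / 1400) = 0.01436
- alternative SE = √((0.20 × 0.80 + 0.15 × 0.85) / 1400) = 0.01433
- (0.05 − 1.96 × 0.01436) / 0.01433 = 1.525, so power is 93.6% (stated: 94%)

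With 59 practices, 59 × 700 / 15 = 2753, or 1377 per side, which gives 93.3% (stated: 93%). The stated power is thus that of the pooled halves, so the pooled contrasts are the natural ones to judge.

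**How far apart the two odds ratios are.** Between-practice variance of the rate is 0.02 × 0.20 × 0.80 = 0.0032. On the logit scale it is about 0.0032 / 0.16² = 0.125. With the usual logistic–normal approximation, the conditional log odds ratio is the marginal one times √(1 + 0.346 × 0.125) = 1.021, where 0.346 = (16√3 / 15π)². For 20% v 15% the marginal odds ratio is (0.15/0.85) / (0.20/0.80) = 0.706, log −0.348. The conditional log is −0.348 × 1.021 = −0.356, an odds ratio of 0.701. With practice effects alone, the target changes by about 2% on the log scale. GP and patient terms would widen the gap by an amount the article gives no figures to compute.

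**Type I error of GEE.** Under no effect, practice rates were drawn from a beta distribution (mean 0.20, ICC 0.02) and practice sizes from a gamma distribution. A logistic GEE was fitted with practice as cluster and baseline rate as covariate. Two runs with different random seeds used 8,000 replicates per setting. The Monte Carlo standard error is √(0.05 × 0.95 / 8000) = 0.24 points at 5% and about 0.35 points at 11%. Ranges are over the three CVs and both runs, in %.

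| Comparison | Working correlation | Sandwich, z | With m/(m−1), z | Kauermann–Carroll, t | Mancl–DeRouen, t |
|---|---|---|---|---|---|
| Table 1 contrast, 59 practices | exchangeable | 6.2–7.4 | 5.9–7.1 | 4.9–5.7 | 4.1–4.7 |
| Table 1 contrast, 59 practices | independence | 6.3–8.3 | 6.2–8.0 | 5.0–6.1 | 4.4–4.6 |
| One group v another, 15 v 14 | exchangeable | 7.5–8.1 | 6.9–7.5 | 4.9–5.5 | 3.7–4.2 |
| One group v another, 15 v 14 | independence | 7.2–11.0 | 6.8–10.4 | 4.7–7.1 | 3.5–5.0 |

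For the Table 1 contrasts, the mean sandwich standard error is 0.94–0.97 of the true standard deviation with an exchangeable structure and 0.91–0.96 with independence. The 11.0% arises only with independence and CV 0.8.

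A further simulation with logit-normal practice effects (6,000 replicates, CV 0.3–0.8) gave 6.5–7.0% (exchangeable) and 7.0–9.4% (independence) for the main effects, and 6.8–7.7% and 7.6–10.3% for one group against another.

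**Adding practice size as a covariate** (log size, CV 0.5 and 0.8, one run) does not remove the inflation. For the Table 1 contrasts the plain z test gives 6.2–7.3% (exchangeable) and 7.4–9.1% (independence). Kauermann–Carroll with t gives 4.8–5.5% and 5.3–6.6%; Mancl–DeRouen with t gives 3.9–4.4% and 4.1–4.6%.

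**The case against.** The strongest reply is that this is a journal article. The type of robust variance, the working correlation and the reference distribution are details it may leave to an analysis plan that is not shown. That stands. A reader might infer that the plan fixes uncorrected errors and so breaks its 5% level. The text says only that the errors are robust, so the inflation applies only if no correction is made. The reply does not cover the choice of model, because there the article does commit itself, twice and differently.

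Three other stronger readings are not supported:

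- A reader might count three competing models. The hierarchical logistic model is given its own task, effects over time, and is itself a mixed model. The conflict is between two frameworks.
- A reader might infer that the GP level cannot be fitted because "patients attending each practice can consult with multiple different GPs over time". The article states no nesting of patients within GPs, and its wording does not exclude cross-classified or multiple-membership terms.
- A reader might attach the 7–11% to the tabulated comparisons. Table 1 lists only pooled contrasts. Comparing any two groups is mentioned for power in Sample size and in the Discussion, so such tests are possible but not tabulated.

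It is also fair to say that the two odds ratios would be numerically close here, and that preferring GEE to a mixed model, or the reverse, is a matter of judgement. Neither point removes the need to choose in advance.

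**Conclusion.** The point holds in a limited form. The formal comparisons are assigned to two frameworks and neither is primary; this follows from the text alone. The difference in estimand is small if only practice effects enter (about 2% of the log odds ratio), so the practical weight lies in which standard error and p-value count.

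Conditional on GEE with standard robust errors and a z test, type I error is about 6–8% for the Table 1 contrasts and about 7–11% for single-group comparisons. The upper ends need independence weighting and very unequal practice sizes. Both ranges rest on the assumed size CV of 0–0.8 and correlation of 0.6. The logit-normal model reached 9.4% for the main effects at its least favourable independence setting. The mixed model's error rate was not examined. This is a modest inflation that is cheap to remove and does not threaten the design.

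**What to change.** 1. Name one primary model for the two Table 1 contrasts and state whether its target is the practice-specific or the population-averaged odds ratio. Make the other model a sensitivity analysis.
2. If GEE is primary: practice as the cluster, exchangeable working correlation, a small-sample-corrected sandwich variance (Kauermann–Carroll or Mancl–DeRouen), and a t reference with degrees of freedom equal to practices minus estimated parameters. With an exchangeable structure Kauermann–Carroll stays closest to 5%; Mancl–DeRouen is slightly conservative. An m/(m−1) factor alone is not enough.
3. Adjust for both minimisation variables, baseline testing rate and practice size. The second is already recorded for every practice. Because it adds a practice-level parameter, pair it with the correction in step 2.
4. If single groups are also to be compared, apply the same correction there, where it matters most.

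The cost is a few sentences in the analysis plan, a few lines of code and slightly wider intervals. No new data are needed. It should be settled before outcome data are analysed.
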